#### Social anxiety

The Social Anxiety Scale for Adolescents (SAS-A) [34] will be employed in the current study to measure social anxiety symptoms. The SAS-A is a 22-item measure that consists of 18 descriptive self-statements assessing the respondent’s subjective experience of social anxiety, and four filler items reflecting activity or social preferences. Each item is rated on a five-point scale ranging from 1 (not at all) to 5 (all the time). A total scale score can be obtained by summing the ratings for the 18 descriptive self-statements, with total scores ranging from 18 to 90. Higher SAS-A scores are indicative of greater social anxiety symptoms. Three subscales can also be derived from the SAS-A which measure fear of negative evaluation (FNE), social avoidance and distress with new social situations or unfamiliar peers (SAD-New), and more generalised social avoidance and distress (SAD-General).

#### Anxiety sensitivity

The Childhood Anxiety Sensitivity Index (CASI) [35] will be administered in the current study to measure symptoms of anxiety sensitivity, which is associated with panic attacks and panic disorder. The CASI consists of 18 items that assess the extent to which the respondent believes that the experience of anxiety will result in negative consequences. Each item is responded to on a three-point scale ranging from 1 (none) to 3 (a lot). Total scale scores are calculated by summing the ratings across all items. CASI scores can range from 18 to 54, with higher scores reflecting greater levels of anxiety sensitivity.

#### Depressive symptoms

Depressive symptoms will be measured on the Center for Epidemiological Studies Depression Scale (CES-D) [36], which consists of 20 items. Respondents indicate the frequency with which they have experienced symptoms during the past week on a four-point Likert type scale ranging from 1 (rarely or none of the time (<1 day)) to 4 (most or all of the time (5 to 7 days)). A total scale score is calculated by summing items scores, after reverse scoring those items that are negatively worded. Total scale scores can range from 0 to 60, with higher scores indicative of more depressive symptomatology.

#### Wellbeing

Mental wellbeing will be assessed by the Warwick-Edinburgh Mental Well-being Scale (WEMWBS) [37]. The WEMWBS is a self-report scale that consists of 14 positively worded items that measure different aspects of positive mental health. Each item is rated on a five-point Likert type scale ranging from 1 (none of the time) to 5 (all of the time), with a total scale score calculated by summing item scores. Total WEMWBS scores can range from 14 to 70, with higher scores indicating a greater level of mental wellbeing.

#### Anxiety stigma

Personal and perceived anxiety stigma will be measured by the Generalised Anxiety Stigma Scale (GASS) [38], which consists of two parallel sets of items. The first set of 10 items is designed to assess the respondent’s personal attitudes to stigma (GASS-Personal); the second set of 10 items measure the respondent’s perception of the attitudes of others (GASS-Perceived). The respondent is asked to rate each item on a five-point scale ranging from 0 (strongly disagree) to 4 (strongly agree). Total GASS-Personal and GASS-Perceived scores are calculated by summing the respective item scores, with total scale scores ranging from 0 to 40. Higher total scale scores are indicative of greater personal or perceived anxiety stigma.

#### Anxiety literacy

Anxiety literacy (A-Lit) [39] was assessed using a 22-item test of anxiety knowledge (for example, sign and symptoms, causes, treatments), which was adapted from the previously developed depression literacy scale (D-Lit) [27]. Each item on the A-Lit is rated on a ‘true/false/don’t know’ scale and is scored by assigning a 1 to each correct response and a score of 0 to each incorrect or ‘don’t know’ response. A total scale score is calculated by summing the item scores. Total scale scores can range from 0 to 22, with higher scores reflecting greater anxiety literacy. We will also assess attitudes to treatments by asking the respondent to rate whether each of the interventions listed are likely to be helpful, harmful or neither for someone with anxiety. This measure was also adapted from a previous measure for depression [40].

#### Help-seeking

Help-seeking attitudes, intentions and behaviours will be measured using the Attitudes Toward Seeking Professional Psychological Help-Short Form (ATSPPH-SF) [41] and an adapted version of the General Help-Seeking Questionnaires (GHSQ) and Actual Help-Seeking Questionnaire (AHSQ) [42]. The ATSPPH-SF is a 10-item measure of attitudes toward seeking psychological help. Each item is responded to on four-point Likert type scale ranging from 0 (disagree) to 3 (agree). A total scale score is calculated by summing items scores, after reverse scoring those items that are negatively worded. Total scale scores can range from 0 to 30, with higher scores indicative of more positive attitudes toward seeking psychological help.

The adapted version of the GHSQ assesses intentions to seek help from 14 different sources (for example, friend, mother, psychologist, teacher) and 13 treatments or activities (for example, CBT, meditation, Internet-based program) for anxiety. Respondents indicate how likely they are to seek help from or use each of the sources or treatments on a scale ranging from 1 (extremely unlikely) to 7 (extremely likely). The adapted AHSQ assesses recent help-seeking behaviour and consists of the same 14 sources of help and 13 treatments or activities for anxiety, which the respondent either does or does not report seeking help from.

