A number of effective school-based prevention and early intervention programs for anxiety have been developed and implemented [19,20]. These programs tend to target current anxiety levels with the aim of preventing anxiety symptoms from worsening or preventing the development of anxiety symptoms at all. Despite their effectiveness, these programs are not routinely delivered in schools. The reasons for the lack of uptake of effective programs are not clear. It is apparent however, that teachers are often not keen to deliver mental health programs in the classroom due to a lack of training or general expertise in the field [21]. Teachers may be anxious about the effect of mental health materials on their students, and may be concerned that they themselves will be unable to handle any consequences. These problems indicate an important need to develop appropriate methods of delivering and implementing effective anxiety intervention programs in schools, particularly if schools are to function as a vector for mental health symptom reduction and prevention. A major concern has also been in the perception that behavioural change needs to be maintained, and that appropriate channels to seek help when required are needed in a comprehensive model.

The aims of the present project, therefore, are two-fold. The first is to test the effectiveness of an online intervention program for anxiety relative to a control condition. The second is to determine whether an enhanced version of the program which incorporates access to a potential service provider results in improved outcomes relative to the standard teacher administered intervention. The anxiety intervention to be evaluated in the current trial is an automated anxiety literacy and cognitive behavioural therapy (CBT) program delivered via the Internet. This program has the potential to overcome some of the problems associated with traditional face-to-face school-based programs by providing a self-directed program to students that requires little teacher training or knowledge. The automated delivery of Internet-based interventions also ensures the fidelity of a program, while its self-directed nature can promote independent learning.

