#### Hypotheses

(1) The e-couch Anxiety and Worry program (whether delivered by the school or the health service method) will be associated with significantly lower levels of generalised anxiety symptoms at post-intervention, 6- and 12-month follow-up, than the wait-list control condition.

(2) The effect of the e-couch Anxiety and Worry program on anxiety symptoms and help-seeking behaviour will be greater in the guided e-GAD health service method than in the e-GAD school method.

(3) The e-couch Anxiety and Worry program (delivered by either method) will be associated with significantly lower levels of depressive symptoms and anxiety stigma, and higher levels of wellbeing, anxiety literacy and help-seeking attitudes, intentions and behaviours at post-intervention, 6- and 12-month follow-up, than participants in the wait-list control condition.

(4) The e-couch Anxiety and Worry program (delivered by either method) will prevent the development of anxiety and depressive symptoms over 12 months in those who are asymptomatic at baseline.

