### Intervention

The e-couch Anxiety and Worry program (http://www.ecouch.anu.edu.au) consists of two major parts: psychoeducation and a series of evidence-based toolkits for anxiety consisting of CBT, relaxation and physical activity. The psychoeducation section is modelled on mental health literacy interventions previously found to improve attitudes and reduce symptoms for depression and anxiety [27,28]. The content of the psychoeducation section is as follows: definition of worry; distinction from stress; differentiation of worry, fear and anxiety; description of anxious thinking; differentiation of GAD from panic disorder (PD), specific phobia and social anxiety disorder (SAD), adjustment disorder and post-traumatic stress disorder (PTSD); description of risk factors for GAD; the problem of co-morbidity; consequences of anxiety; and treatments for anxiety including medical, psychological and lifestyle treatments. The content of these sections is based on reviews of evidence of alternative and lifestyle treatments [29] and on clinical practice guideline [28].

The CBT toolkit for anxiety is based on previously developed material with confirmed efficacy for anxiety cognitions and beliefs in at-risk individuals [30,31]. This toolkit teaches participants about worry, what causes and compounds worry, how to detect and reduce worry, how to problem solve the issues causing worry, how to change thoughts to prevent and reduce worry, and exploring the feelings behind worry. This toolkit essentially focuses on the cognitive aspects of worry and how to change them. The vast majority of school-based prevention programs for anxiety are based on CBT techniques such as these and have been found to be both efficacious and safe [19,20].

The relaxation toolkit contains a mindfulness meditation exercise and progressive muscular relaxation exercise. In the mindfulness meditation exercise participants are encouraged to focus on their breathing and to be in the present moment, rather than lost in thoughts, memories or the future. Mindfulness meditation promotes a sense of calm. Progressive muscular relaxation involves tensing and relaxing the different muscle groups in the body. This exercise helps participants to recognise the tension in their bodies and how to relieve it.

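### The adapted AHSQ counts CBT, meditation and Internet-based programs as help-seeking behaviour; both intervention arms receive these in class, so allocation alone can raise the score against wait-list

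*Protocol article*

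**What the plan says.** **The measure.** The Help-seeking section of the Protocol article describes the adapted GHSQ (intentions) as covering 14 sources of help and "13 treatments or activities (for example, CBT, meditation, Internet-based program) for anxiety". It then reuses both lists for behaviour: "The adapted AHSQ assesses recent help-seeking behaviour and consists of the same 14 sources of help and 13 treatments or activities for anxiety". That makes 14 + 13 = 27 items. Each takes a yes/no answer, being described as one "which the respondent either does or does not report seeking help from". Three of the 13 treatments are named; the other ten are not listed. No total score or recall window is given for the AHSQ, beyond saying that the behaviour is recent.

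**The intervention.** The Background calls e-couch an "automated anxiety literacy and cognitive behavioural therapy (CBT) program delivered via the Internet". The Intervention section describes "a series of evidence-based toolkits for anxiety consisting of CBT, relaxation and physical activity" and adds: "The relaxation toolkit contains a mindfulness meditation exercise". Under Procedure, both intervention arms do the program in a weekly class over six weeks. Wait-list schools keep their usual classes and are offered e-couch only once the 12-month questionnaire is done.

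**The claim to be tested.** Against wait-list, Hypothesis 3 predicts "higher levels of wellbeing, anxiety literacy and help-seeking attitudes, intentions and behaviours at post-intervention" and at both follow-ups, as well as lower depressive symptoms and stigma. Secondary aim 2 also lists help-seeking behaviour as an outcome.

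**The concern.** An outcome that records whether a student has used CBT, meditation or an online program overlaps with a treatment made up of CBT, meditation and an online program. The overlap differs by arm: intervention students are exposed by timetable and wait-list students are not. An intervention student who ticks one of these items because of the lesson adds to measured help-seeking without having sought any help. No section tells respondents or analysts to leave the allocated program out.

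What is at stake is the meaning of a positive result. A higher AHSQ score than wait-list could reflect students seeking more help, or students recording that they were in the lesson, and the total would not separate the two. The error runs in favour of the intervention. Help-seeking is part of the stated rationale for working in schools, so a misread result here would matter even though the outcome is secondary.

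**Working it through.** **1. Match of items to program content**

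| AHSQ treatment named | Delivered by e-couch? | Where stated | Wait-list exposure during the trial |
|---|---|---|---|
| CBT | Yes, CBT toolkit | Background; Intervention | None assigned |
| Meditation | Yes, relaxation toolkit | Intervention | None assigned |
| Internet-based program | Yes, e-couch itself | Background; Procedure | None assigned |

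All three named treatments match, which is 3 of 13 treatments and 3 of 27 items. The ten unnamed treatments cannot be checked.

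**2. What size could this have?** The article gives no figure for the AHSQ, so there is nothing to reproduce directly. The plan's own sample-size figures supply the number of students:

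- Design effect: 1 + (25 − 1) × 0.02 = 1.48, as stated.
- Effective sample: 525 / 1.48 = 354.7; the article states 354.
- Per arm, assuming equal arms: 354 / 3 = 118.

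This borrows the plan's ICC for an outcome whose ICC is not given.

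**3. One item analysed alone (assumed rates).** Let p0 be the control rate. Let q be the share of intervention students, among those who would not otherwise tick the item, who tick it because of the lesson. Then p1 = p0 + q(1 − p0). For example, 0.05 + 0.10 × 0.95 = 0.145. The table gives the chance of a two-sided 5% result, 118 against 118, with no true change in help-seeking (normal approximation for two proportions).

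| p0 | q = 10%: p1, chance | q = 20%: p1, chance |
|---|---|---|
| 5% | 14.5%, 69% | 24%, 99% |
| 10% | 19%, 50% | 28%, 95% |
| 20% | 28%, 30% | 36%, 79% |

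If both intervention arms are pooled against wait-list (236 against 118), the first cell rises from 69% to 79%.

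**4. A count over all 27 items (assumed SD of 2 to 5 items).** Here q is the share of intervention students who add all three items because of the lesson. The shift is 3q items and d = 3q / SD.

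| q | Shift (items) | d, SD 2 to SD 5 | Chance of significance |
|---|---|---|---|
| 10% | 0.3 | 0.15 to 0.06 | 21% to 7% |
| 25% | 0.75 | 0.375 to 0.15 | 82% to 21% |
| 50% | 1.5 | 0.75 to 0.30 | about 100% to 64% |

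The artefact can thus be negligible or decisive. It depends on how the score is built and how students read the items, and the article settles neither.

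**The case against.** Several points on the other side have force.

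- **Scoring is not stated and may sit in an analysis plan that is not shown.** True, and an analysis limited to the 14 sources would avoid the problem. But the point does not rest on a missing scoring rule. The article fixes the instrument's content, and that content includes the treatment.
- **The items ask about seeking help for anxiety.** A student sitting a compulsory lesson could truthfully answer no. This stands as a reason for doubt about size, since the questionnaire stem is not shown. It does not remove the risk: on a single item with a low control rate, a small share of lesson-driven answers is enough.
- **The behaviour asked about is recent.** The lessons may fall outside the recall window at 6 and 12 months. This stands. Post-intervention is the clearest exposure, and the later occasions are probably less affected.
- **Program use is measured elsewhere.** The Satisfaction and Adherence sections record use of e-couch strategies and log completed modules. That helps interpretation, but nothing there links these records to the AHSQ.
- **The assumed rates and SDs have no source in the article.** Correct; they show a range and estimate nothing. The plan's 0.3 SD target concerns generalised anxiety symptoms and is not a yardstick for help-seeking.

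A reader might also infer that attending class could satisfy Hypothesis 3 as a whole. The article does not support that. The hypothesis also covers depressive symptoms, stigma, wellbeing, literacy, attitudes and intentions, none of which is measured by the AHSQ.

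**Conclusion.** The concern holds for one component: help-seeking behaviour against wait-list, in Hypothesis 3 and secondary aim 2, and most clearly at post-intervention. The item overlap and its difference by arm follow from the text without any assumption. The size does not. Under the assumptions shown, it runs from 0.06 SD on a 27-item count to a near-certain false positive on a single item. Endorsement rates, SD, scoring and recall window would all be needed to narrow that.

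Three wider readings are not supported:

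- **Hypothesis 2.** The school and health-service arms both receive e-couch, so the overlap largely cancels in that contrast.
- **GHSQ intentions.** Greater willingness to use CBT or an online program in future is a legitimate effect of the intervention; attendance does not produce it mechanically.
- **The primary outcome.** Generalised anxiety symptoms are measured by other scales and are untouched.

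The point is worth acting on. The error has one direction, and it can be avoided by how the items are scored.

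**What to change.** Before the arms are compared on this outcome, state that help-seeking behaviour in the wait-list comparison is the score on the 14 AHSQ sources of help. An alternative is the 27-item list after removing every item that e-couch delivers: CBT, meditation, Internet-based program, and any of the ten unnamed treatments that prove to match program content. Report the removed items separately by arm and occasion, labelled as possible programme exposure.

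The cost is a scoring rule applied to items the questionnaire already collects. The downside is a shorter score that misses genuine self-initiated use of online programs, CBT or meditation; that use stays visible in the separate report.

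No change is needed to the GHSQ intentions score or to the active-versus-active contrast. The questionnaire wording should also stay as it is: Trial status reports recruitment complete and data collection under way, and a change of stem would break comparability with the pre-intervention answers.

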#### Disability

Disability caused by anxiety symptoms will be assessed using a four-item open-ended measure of the number of full and partial days out of role in the past 30 days due to anxiety.

#### Satisfaction

Participant satisfaction with the e-couch Anxiety and Worry program will be measured through an assessment of individual usage of the program and its perceived usefulness using measures developed for previous ANU online trials. Example items will include ‘How much did you learn from the website?’, ‘Do you think you will use the website in the future?’ and ‘Would you recommend the website to others?’ Participant use, and the perceived helpfulness, of the strategies and techniques taught in the e-couch Anxiety and Worry program will also be individually assessed, as will participant knowledge and use of *headspace* mental health services.

#### Adherence

Participant adherence to the program will be measured by the number of program modules and exercise completed, which will be automatically recorded by the software of the e-couch Anxiety and Worry program. A number of potential predictors of adherence will also measured in the current study. These will include the perceived efficacy of Internet-based interventions (for example, ‘I am confident that people could learn skills for preventing anxiety from a website’), Internet literacy (for example, ‘I am confident in my ability to use the Internet’), motivation (for example, ‘rate the importance of preventing an episode of clinical anxiety over the next year’), and behavioural intentions (for example, ‘I want to change the way I think and feel about emotional problems’).

### Sample size and power calculations

Assuming an average class size of 25, a total of 750 students will be available in 30 classes. Based on our previous work [24], we anticipate an intraclass correlation (ICC) of 0.02 and non-participation rate of 30%, with 5% of this non-participation/completion arising from students leaving the school or being absent on measurement occasions. The majority of non-participation (estimated at 25%) will result from failure to return parental consent forms resulting in an inability to participate in the study. In the current study, we plan to address this problem by using electronic communication with parents. We anticipate that this will result in data from 525 students being available. The ICC of 0.02 leads to a design effect of 1.48 and an effective sample size of 354. Assuming a correlation between measurements over time of 0.5, two-tailed tests and alpha of .05, the trial would have 80% power to detect group differences down to 0.3 standard deviations. A group difference of 0.3 standard deviations is marginally higher than the effects obtained using MoodGYM as a universal intervention but, as the current intervention is specifically aimed at anxiety, a slightly larger effect can be reasonably expected. The magnitude of the incremental effect arising from adding *headspace* support to the e-GAD school method condition is uncertain. Comparison of the school method and health service method conditions could be conceptualized within a non-inferiority framework [43] however the sample size required using a defensible non-inferiority margin would be unfeasible. Given the additional costs and resources associated with providing health service support, it was considered acceptable to power the trial to be able to detect differences between the two active conditions comparable in magnitude to comparisons with the wait-list control condition.

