### Recruitment

At least 30 schools from across Australia will be recruited to participate in the trial. Schools will be drawn from rural and metropolitan areas and male and female adolescents in grades 9 to 12 (aged 14 to 18 years) will be invited to participate. Schools will be recruited according to the location of participating *headspace* centres. Information letters will be sent to each school informing them of the project. A briefing day will be held for all participating schools prior to the trial’s implementation. The briefing day will provide schools with an opportunity to meet other schools involved in the trial and to receive detailed information and instruction on the delivery of the trial. Information and consent forms will be distributed to all invited participants and their parents/guardians, with written informed consent required from both.

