### Randomisation

Each participating school (cluster) will be randomised to one of the three conditions. Randomisation will occur according to *headspace* centre location. Cluster randomisation will be employed for administrative convenience, to avoid wait-list control condition contamination, and for the ecological validity of providing the intervention at the cluster level [25,26]. A statistician not involved in the implementation of the trial will randomly allocate schools within each *headspace* centre to the intervention or wait-list control conditions using a computerised random number generator. The identity of schools will be concealed from the statistician during this process.

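### The design effect of 1.48 uses the full class of 25, but it divides the 525 students left after losses (17.5 per cluster), so the effective sample size of 354 does not follow from the plan's inputs

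*Protocol article*

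**What the plan says.** All the inputs stand in one paragraph of the protocol article, under Sample size and power calculations. It starts from full classes: "Assuming an average class size of 25, a total of 750 students will be available in 30 classes". It then sets the clustering and loss assumptions: "we anticipate an intraclass correlation (ICC) of 0.02 and non-participation rate of 30" per cent. Of that loss, 25 percentage points are attributed to parental consent forms that are not returned, and 5 to students who leave the school or are absent when measurements are taken. The result is: "We anticipate that this will result in data from 525 students being available". The paragraph then concludes: "The ICC of 0.02 leads to a design effect of 1.48 and an effective sample size of 354".

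The power statement follows. It rests on "Assuming a correlation between measurements over time of 0.5, two-tailed tests and alpha of .05" and claims that "the trial would have 80% power to detect group differences down to 0.3 standard deviations".

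Two other sections define the cluster. Recruitment says: "At least 30 schools from across Australia will be recruited to participate in the trial". Randomisation says: "Each participating school (cluster) will be randomised to one of the three conditions". Thirty classes and at least 30 schools together imply one class per school, although the article does not say this outright.

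**The concern.** A design effect measures how much clustering inflates the variance among the students who supply data. Its cluster size must therefore be the mean number analysed per cluster. Here the total has been reduced for losses and the cluster size has not. Most of the lost students never return a consent form and cannot enter any analysis, so on the plan's own assumptions an average of 25 analysed students per cluster cannot occur.

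At stake is the accuracy of a stated planning figure. The effective sample size of 354 is the basis for the claim of 80% power at 0.3 SD, and a reader who tries to verify that claim will start from a number that the plan's inputs do not give.

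**Working it through.** **Inputs** (Sample size and power calculations): 30 classes, 25 students per class, 30% non-participation, ICC 0.02, correlation over time 0.5, two-sided alpha 0.05, target difference 0.3 SD.

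**Formulae.** Design effect = 1 + (m − 1) × ICC, where m is the mean number analysed per cluster. Effective N = N / design effect.

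**The plan's figure reproduced**
- Students with data: 750 × 0.70 = 525.
- With m = 25: 1 + 24 × 0.02 = 1.48.
- 525 / 1.48 = 354.7, stated as 354.

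So the plan combined m before losses with N after losses.

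**Consistent pairings**
- Both after losses: m = 525 / 30 = 17.5; design effect = 1 + 16.5 × 0.02 = 1.33; effective N = 525 / 1.33 = 394.7.
- Both before losses: m = 25 and N = 750; effective N = 750 / 1.48 = 507.
- If only the 25% consent loss is taken off the cluster size, m = 18.75; design effect = 1 + 17.75 × 0.02 = 1.355; 525 / 1.355 = 387.

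None of these gives 354. The after-loss value exceeds 354 by a factor of 394.7 / 354 = 1.115.

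**Unequal cluster sizes.** With a coefficient of variation CV, design effect = 1 + [(1 + CV²) × 17.5 − 1] × 0.02. The document gives no CV, so these values are assumptions:

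| CV | Design effect | Effective N |
|---|---|---|
| 0 | 1.33 | 395 |
| 0.3 | 1.36 | 386 |
| 0.4 | 1.39 | 379 |
| 0.5 | 1.42 | 370 |

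To reach 1.48 at a mean of 17.5, (1 + CV²) × 17.5 must equal 25, so CV = √(25/17.5 − 1) = 0.65.

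**Effect on power.** The allocation ratio is not stated; 1:1:1 is assumed, which gives 354 / 3 = 118 or 394.7 / 3 = 131.6 effective students per arm. For a comparison of two arms, power = Φ(0.3 / [s√(2/n)] − 1.96). The value of s (in SD units) depends on how the outcome is used, with correlation 0.5:

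| Outcome used | s | Power at 354 | Power at 395 |
|---|---|---|---|
| One occasion, unadjusted (or change score) | 1 | 63.5% | 68.2% |
| One occasion, baseline-adjusted | √0.75 | 75.8% | 80.2% |
| Mean of three post-baseline occasions | √(2/3) | 80.6% | 84.6% |

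The difference detectable with 80% power at one occasion falls from 0.365 to 0.345 SD unadjusted, and from 0.316 to 0.299 SD baseline-adjusted.

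**The case against.** The best defence is that 1.48 is a safe figure. The article gives an average class size, so sizes vary, and consent losses would plausibly differ between schools. Keeping the full class size leaves some margin for that. Some absent students may also still contribute data, because the mixed model keeps participants with missing occasions. This much stands: 395 is the upper value for a mean of 17.5, and restating it without its assumptions would put a best case in place of a cautious one. But the article presents 1.48 as following directly from the ICC and does not mention variation in cluster size. A coefficient of variation of about 0.65 would be needed to justify it in full.

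Two stronger readings are tempting, and the document supports neither. A reader might infer that the trial is underpowered because of this error, or that the error hides a shortfall in power. The direction is the opposite: an effective sample size that is too small understates power, so correcting it narrows any shortfall at a single occasion. A reader might also infer that the whole plan inherits a wrong number. In fact the only stated claim that depends on 354 is the power claim, and it holds with 354 on one reading, the mean of three post-baseline measurements (80.6%).

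Finally, Trial status reports that recruitment was completed in June 2012, so the correction cannot change enrolment. That limits the practical consequence but does not make the figure right.

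**Conclusion.** The stated effective sample size is wrong on the plan's own inputs. It divides the after-loss count by a design effect that belongs to the before-loss class size. The consistent values are a design effect of 1.33 and an effective sample size of about 395, or about 132 per arm under an assumed 1:1:1 allocation. They rest on 30 clusters of equal size and one class per school. A school that supplied more than one class would need its own analysed count, because the school is the randomised cluster.

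This is a modest, conservative error in reporting. The claim of 80% power at 0.3 SD is not overturned. The reading most sensitive to the correction is the baseline-adjusted comparison at one occasion, where power moves from about 76% to about 80%.

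**What to change.** Rewrite the design-effect sentence to give the mean number of students analysed per randomised school (17.5), the design effect (1.33) and the effective sample size (about 395), and state that these assume equal clusters and one class per school. Carry the new figure into the power statement. If 1.48 was kept on purpose as an allowance for unequal clusters, keep it, say so, and give the variation in cluster size that it is meant to cover.

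The cost is one corrected sentence and a recalculated power figure. No change to enrolment, design or analysis is needed.
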